### Aims and objectives

The overall aim of this study is to investigate the clinical relevance of early identification and adequate treatment of sleep disorders that co-occur with mental disorders.

The primary objectives of the study are to investigate:

1) The prevalence of the different six categories of sleep disorders (insomnia, SRBD, hypersomnia, CRSD, parasomnias, and sleep-related movement disorders) in connection to specific mental disorders.

2) Whether screening for and early treatment of sleep disorders exerts positive effects on sleep, treatment outcomes (symptom severity/remission of mental disorder), and quality of life.

Sex differences in both sleep and mental disorders are common; therefore, the effect of sleep disorder treatment may differ between the sexes. Based on this, a secondary objective of this study is to investigate whether there is an interaction effect between sex and treatment of sleep disorders on sleep, mental disorders symptoms (symptom severity/remission of mental disorder), and quality of life.

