### Study population

All treatment seeking individuals who are newly registered at GGZ Drenthe Mental Health Institute (GGZ Drenthe, Assen, NL; https://ggzdrenthe.nl/) will be asked to participate in this study by their treating therapist. The population of this mental health institute consists of individuals diagnosed with a variety of mental health disorders. Most individuals are diagnosed with chronic and/or complex mental disorders and often present with co-morbid disorders. Based on the participants’ main diagnosis according to the *Diagnostic and Statistical Manual of Mental disorders -* Fifth edition (DSM–5) [20], participants will be subdivided into the following diagnostic groups: depressive disorder, bipolar disorder, anxiety disorder, PTSD, attention deficit (hyperactivity) disorder (AD(H)D), autism spectrum disorder (ASD), schizophrenia spectrum disorder (SSD), or personality disorder. Patients under the age of 18, unable to adequately read or speak Dutch, and/or deemed unfit (by their therapist) to fill out questionnaires will be excluded from the study.

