### Study outcomes

Primary outcomes are 1) the prevalence of different sleep disorders as a function of individuals’ mental disorders (depressive disorder, bipolar disorder, anxiety disorder, PTSD, AD(H)D, ASD, SSD or personality disorder), and 2) the effect of sleep interventions on sleep, severity of specific symptoms of mental disorders, general functioning, and quality of life. Secondary outcomes are 1) the effects of sleep interventions on objective outcome parameters, for example use of sleep/sedative medication, number of hospitalizations and length of stay and, 2) differences between genders in the prevalence of specific sleep disorders and sleep intervention effects.

First, we expect that the prevalence of most sleep disorders among individuals with mental disorders will exceed those in the general population. Second, concerning the adjusted sleep interventions, we expect that the treatment of sleep disorders, tailored to mental disorders, will improve sleep, recovery from mental disorder symptoms, and quality of life in most patients. We hypothesize that the effect of added sleep intervention(s) will be larger than the effect of TAU alone in the TAU-SI-T1 group.

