#### Prevalence

Descriptive statistics will be used to assess the prevalence of the different sleep disorders over the entire study population and within different subgroups of mental disorders. The prevalence of the six different types of sleep disorders (based on the HSDQ indicated diagnosis) will be calculated as a frequency for the total study population and for the eight mental disorder diagnostic groups separately. Differences in prevalence between the various mental disorder diagnostic groups will be computed using chi-square and/or Phi or Cramer-V analysis. The Standardized incidence ratio (SIR) will be calculated for the clinical population relative to reported prevalence of the different sleep disorders in the general population.

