#### Effect of sleep disorder treatment

Nearly all sleep disorders induce disturbed sleep and consequently result in a sleep deficit. We hypothesize that the sleep deficit, rather than the underlying disorder, may be most influential on the added burden of the sleep disorder on the patient’s mental well-being. Therefore, in the analysis of the effects of added sleep interventions, no distinction will be made between the different all types sleep disorders and all treatments will be lumped together. The effects of added sleep intervention in all participants with a sleep disorder will be assessed at six and twelve months by comparison of treatment (TAU-SI-T0 and TAU-SI-T1) groups over time (T0, T1, and T2). Secondary analysis will focus on the interaction between treatment effect and sex differences. For statistical evaluation linear mixed models, separate for all outcome parameters, will be employed. A stepwise approach will be followed in which first results for crude models will be taken, after which models including potential confounders such as age, sex, and social demographic parameters are run.

These analyses will be performed in the total population for the quality of life and general symptom outcome parameters, and in the eight mental disorder diagnostic subpopulations (depressive disorder, bipolar disorder, anxiety disorder, PTSD, AD(H)D, ASD, SSD and personality disorder) for the specific mental disorder symptom parameters. Due to power limitations, secondary analysis will only be performed within the more prevalent disorders: depression and PTSD.

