## Discussion

The overarching objective of this project is to develop and evaluate a procedure for early detection and treatment of sleep disorders in individuals with mental disorders in order to augment therapeutic outcome and enhance well-being.

The first aim of this study is to gain insight into the prevalence of the different sleep disorders as a function of specific mental disorders. If we would observe a high prevalence of a certain sleep disorder in connection to a particular mental disorder, extra attention can be paid and extra resources could be allocated to the detection and treatment of that specific sleep disorder within individuals who are diagnosed with this particular mental disorder. Additionally, the observation of a high prevalence of a certain sleep disorder in individuals with a specific mental disorder profile could lead to the identification of novel etiological pathways underlying the respective sleep disorders. This may improve mental health care and provide novel therapeutic targets.

The second aim of this project is to test whether sleep disorder treatment can improve the outcome of common treatment for mental disorders, as well as individual’s quality of life. For some mental disorders, treatment of a co-occurring sleep disorder might significantly improve mental well-being, whereas for other disorders it might have less incremental effects. That treatment of sleep disorders can improve mental health of individuals with mental disorders became evident in studies investigating treatment of insomnia in individuals with depressive disorder [15–18]. However, for other mental disorders and other sleep disorders, the importance of sleep disorder treatment for treatment outcome has only rarely been investigated. Thus, the current project will provide important complementary data allowing evaluation of the clinical relevance of treating sleep disorders in the context of distinct mental disorders.

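### The between-diagnosis prevalence comparison is planned only as a crude test, so differences may partly reflect sex mix and cannot alone support disorder-specific or etiological readings

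*Protocol article*

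**What the plan says.** In the protocol article, Statistical analyses, Prevalence, the frequency of each HSDQ-indicated sleep disorder "will be calculated as a frequency for the total study population and for the eight mental disorder diagnostic groups separately". For the contrast between diagnoses it says: "Differences in prevalence between the various mental disorder diagnostic groups will be computed using chi-square and/or Phi or Cramer-V analysis". No covariate or stratification is named. The same section adds a standardised incidence ratio, but against the general population and not between diagnoses.

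Aims and objectives states: "Sex differences in both sleep and mental disorders are common; therefore, the effect of sleep disorder treatment may differ between the sexes". Study outcomes lists as a secondary outcome "differences between genders in the prevalence of specific sleep disorders and sleep intervention effects". Under Effect of sleep disorder treatment, a crude mixed model is followed by a step in which "models including potential confounders such as age, sex, and social demographic parameters are run". That step belongs to the randomised contrast.

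The Discussion gives the prevalence results two uses. One is directing attention and resources to particular patient groups. The other is that a high prevalence in one disorder profile "could lead to the identification of novel etiological pathways underlying the respective sleep disorders". The Background makes a similar conditional statement.

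**The concern.** A factor related both to the grouping variable and to the outcome confounds a non-randomised comparison. By the article's own premise, sex may be such a factor: it differs between mental disorders and between sleep disorders. Chi-square, Phi and Cramer's V on simple frequencies cannot take it into account. Adjustment is planned for the randomised contrast, where allocation already balances such factors in expectation. It is not planned for the observational contrast, where it matters more.

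At stake is how a primary outcome is read. If one diagnosis shows more of a given sleep disorder, the crude analysis cannot tell whether this goes with the diagnosis or with the proportion of women among those who have it. For resource planning this does not matter. For a claim about a specific pair of disorders, or a pathway, it does.

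**Working it through.** The plan gives no figure for this comparison: alpha and power are stated only for the treatment effect. There is therefore nothing to reproduce, and the check asks how large the distortion could be.

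**Group sizes.** The number to be screened is not stated. Table 2 allows an approximation: required number ÷ percentage of population needed ÷ prevalence.
- Depression: 92 / 0.150 / 0.17 = 3,608.
- Bipolar disorder: 48 / 0.444 / 0.03 = 3,604.
- Seven of the eight rows give 3,587 to 3,628; PTSD gives 3,389.

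With 3,600 and Table 2 prevalences summing to 69%, the eight groups hold 0.69 × 3,600 = 2,484 people. A third of that (828) and the randomised target (472) were also tried.

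**Assumed, not in the article.**
- Share of women, strong imbalance: depression 60%, bipolar 55%, anxiety 60%, PTSD 65%, AD(H)D 40%, ASD 30%, SSD 30%, personality disorder 65%.
- Share of women, mild imbalance: 45% to 55%.
- Sleep-disorder rates for women/men: 40/35, 40/30, 25/15 and 15/30%.
- Within each sex the rate is the same in every diagnosis, so there is no true diagnosis effect.

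**Spurious spread.** Group prevalence = w × (rate in women) + (1 − w) × (rate in men), with w the share of women. At w = 0.30 and w = 0.65:
- 40/35: 36.5% and 38.25%, about 1.7 points.
- 40/30: 33.0% and 36.5%, 3.5 points.
- 25/15: 18.0% and 21.5%, 3.5 points.
- 15/30: 25.5% and 20.25%, about 5.3 points.

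Under mild imbalance, 40/30 gives 34.5% and 35.5%, a spread of 1 point.

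**False rejection at alpha 0.05.** There were 2,000 simulated 8 × 2 tables per scenario. Crude Pearson chi-square is compared with a sex-stratified generalised Cochran-Mantel-Haenszel test (crude / stratified, strong imbalance):

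| Rates, women/men | n = 2,484 | n = 828 | n = 472 |
|---|---|---|---|
| 40/35 | 7.4% / 6.1% | 5.6% / 5.2% | 4.9% / 4.9% |
| 40/30 | 11.3% / 5.6% | 6.4% / 5.1% | 5.7% / 4.9% |
| 25/15 | 14.6% / 5.7% | 6.8% / 4.8% | 5.8% / 4.6% |
| 15/30 | 29.3% / 4.0% | 11.7% / 5.0% | 9.8% / 5.2% |

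With mild imbalance (40/35 and 40/30, n = 2,484 and 472) the crude rate was 4.5% to 5.2%. The simulation error of a 5% rate is √(0.05 × 0.95 / 2,000) = 0.5 points.

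**Analytic check of the largest cell.** Noncentrality λ = Σ n(p − P)² / [P(1 − P)], with P the pooled prevalence. For 15/30 at n = 2,484, P = 0.218 and λ = 4.95, so Cramer's V = √(4.95 / 2,484) = 0.045. A noncentral chi-square with 7 degrees of freedom then rejects in about 31%, in line with the simulated 29.3%.

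**The case against.** The strongest reply is that the planned analysis fits its aim. The section describes itself as descriptive, and crude prevalence is the right quantity for deciding where to look for sleep disorders. The etiological remarks are conditional and stand outside the analysis section, and no causal estimand is declared. All of this stands. It limits the point to how differences are interpreted and leaves the crude results valid for what they describe. But even generating hypotheses about particular pairs of disorders requires separating diagnosis from sex mix.

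The sentence on sex differences is offered as a reason for effect modification by sex, and it carries no figures. That is fair, but the stated premise is a link of sex with both kinds of disorder, which is also the condition for confounding. The gender outcome will show part of the sex pattern without adjusting the contrast between diagnoses.

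A reader might infer that demographic differences are bound to surface as false links and that the chi-square would usually be significant. The article does not support this. Take an assumed base risk of 8%, doubled in men, and groups that are 65% and 30% male. The prevalences are 0.08 × (0.65 × 2 + 0.35) = 13.2% and 0.08 × (0.30 × 2 + 0.70) = 10.4%. A two-group chi-square then rejects in about 16% (140 versus 600 patients) to 25% (315 versus 600). It reaches 69% to 89% only if risk is also assumed to double with older age and the groups are 55% and 20% older: 0.132 × 1.55 = 20.5% and 0.104 × 1.20 = 12.5%. The article lists age as a potential confounder of the treatment effect, but nowhere says that it is linked to both diagnosis and sleep disorder.

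Supplementary models are often left to an analysis plan, which is not shown. Here, however, the article fixes the method for a primary outcome, and it does describe adjustment where it intends it.

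**Conclusion.** The point holds in limited form. The between-diagnosis comparison is crude, nothing else in the article adjusts it, and the article's own premise makes sex a possible confounder. Differences may partly reflect sex mix. That age mix also contributes is an assumption.

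Under the assumed inputs, sex alone produces spurious spreads from 1 point or less to about 5 points. The excess of false rejections ranges from none to about 24 percentage points (29% against 5%), the latter only with strong imbalance, a twofold sex difference in rates and about 2,484 patients. The actual size cannot be determined from the article.

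A reader might also infer that the crude test is invalid or must be dropped. It is not: it is a correct test of crude prevalences. What it cannot carry alone is a disorder-specific or etiological interpretation. This is an inexpensive improvement to the plan.

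**What to change.** Keep the crude prevalences and the chi-square, labelled as descriptive. For each HSDQ category, add a regression (logistic or modified Poisson) on main diagnosis, sex and age, or report sex- and age-standardised prevalences per diagnosis with 95% confidence intervals. State that any claim about a specific link between a sleep disorder and a mental disorder rests on these adjusted results.

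The cost is minor analysis work and slightly wider intervals in the small groups. Age and sex are already needed for the planned treatment models, and main diagnosis already defines the groups; the two covariates must be available for everyone screened, including those below the HSDQ cut-off.

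A further model with comorbid diagnoses is optional. Study population says that patients "often present with co-morbid disorders", but the article groups by main diagnosis and does not show that comorbid diagnoses are recorded in structured form. Adjusting for them would also answer a different question.

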#### Effect of sleep disorder treatment

Nearly all sleep disorders induce disturbed sleep and consequently result in a sleep deficit. We hypothesize that the sleep deficit, rather than the underlying disorder, may be most influential on the added burden of the sleep disorder on the patient’s mental well-being. Therefore, in the analysis of the effects of added sleep interventions, no distinction will be made between the different all types sleep disorders and all treatments will be lumped together. The effects of added sleep intervention in all participants with a sleep disorder will be assessed at six and twelve months by comparison of treatment (TAU-SI-T0 and TAU-SI-T1) groups over time (T0, T1, and T2). Secondary analysis will focus on the interaction between treatment effect and sex differences. For statistical evaluation linear mixed models, separate for all outcome parameters, will be employed. A stepwise approach will be followed in which first results for crude models will be taken, after which models including potential confounders such as age, sex, and social demographic parameters are run.

These analyses will be performed in the total population for the quality of life and general symptom outcome parameters, and in the eight mental disorder diagnostic subpopulations (depressive disorder, bipolar disorder, anxiety disorder, PTSD, AD(H)D, ASD, SSD and personality disorder) for the specific mental disorder symptom parameters. Due to power limitations, secondary analysis will only be performed within the more prevalent disorders: depression and PTSD.

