### Procedure

As part of the intake procedure of the mental health institute, routine outcome assessment (ROA) measurements are conducted in most departments of the institute, using an established online platform [21]. We will use this infrastructure, to reduce the burden to the participants and ensure data quality. Participants will be asked to complete questionnaires prior to the intake procedure (T0), 6 (T1), and 12 (T2) months later.

To screen for sleep disorders, patients fill out the Holland Sleep Disorders Questionnaire (HSDQ) [22, 23]. Patients who score above the cut-off score for any specific category of sleep disorders will be invited to participate in this study. After being informed about the study procedures, they will be asked for informed consent.

For both the experimental and control conditions, participants will continue their treatment as usual (TAU) throughout the study. After stratification for type of mental disorder, participants will be randomly assigned (using Sealed Envelope software) to either the experimental or control condition. In the experimental condition sleep intervention(s) (SI) will start immediately at T0 (TAU+SI-T0). In the control condition, the sleep intervention(s) will first start six months after inclusion, at T1 (TAU+SI-T1). This allows to test the effects of early interventions for sleep disorders on mental disorder symptoms, general functioning, sleep, and quality of life. Sleep interventions generally start with extensive diagnostic evaluation, followed by patient-targeted sleep treatment. For individuals scoring below the cut-off score for a sleep disorder on the HSDQ, participation is limited to filling out the questionnaires at T0. An exception to randomised allocation will be made for participants in the control condition whose HSDQ result or intake interview indicates a very severe sleep disorder, such as Narcolepsy. These participants will be immediately referred to a sleep centre, regardless of original randomization. These patients will be included in the prevalence estimate, but excluded from the analysis of the treatment effects. An overview is provided in Fig. 1.

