##### Positive and negative syndrome scale (PANSS)

In addition to the “PHAMOUS-basis psychosevragen”, in individuals with a SSD diagnosis assessments will be made on positive and negative symptoms at T0 and T2 as part of the ROM, using the Positive and Negative Syndrome Scale (PANSS) [39] interview. The PANSS is a validated 7-point, 30-item rating instrument, with each point representing increasing levels of psychopathology: 1 = “absent”, 2 = “minimal”, 3 = “mild”, 4 = “moderate”, 5 = “moderate-severe”, 6 = “severe”, and 7 = “extreme” [39].

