### Sample size calculations

Power analysis were performed using G*Power software [45]. Based on previous studies [18, 46], we aim at an effect size of 0.4 (Cohen’s d) for the outcome variables “quality of life”, “general functioning” and “mental disorder specific symptoms”. Power analysis based with an α of .05 and a power of .8, resulted in a required group size of 48 patients per diagnostic group (24 TAU+SI-T0 and 24 TAU+SI-T1). Due to limitations in recruitment capacity in less prevalent disorders, differences across both sexes will only be examined in the relatively high prevalent disorders: depression and PTSS. Power analysis with a 2 × 2 experimental group design (TAU+SI-T0 versus TAU+SI-T1; and males versus females) as between subject factors and the three time points as within subject factors suggests that with an α of .05 and a power of .8 a group size of 92 per group (46 TAU+SI-T0 and 46 TAU+SI-T1) would be sufficient. This analysis assumes an equal sex distribution. Overall, a total of 472 participants will be included in this study (overview provided in Table 2).

**Table 2 Tab2:** *Overview of targeted sample-sizes per diagnostic category*

Group	Prevalence (%)	Sec. analysis: yes/no	Required number per experimental group	Total required number per diagnostic subgroup	% of total population needed to include
**Depression**	17	Yes	46	92	15.0
**Bipolar disorder**	3	No	24	48	44.4
**Anxiety disorder**	10	No	24	48	13.3
**PTSD**	15	Yes	46	92	18.1
**ADHD/ADD**	9	No	24	48	14.7
**ASD**	4	No	24	48	33.1
**SSD**	5	No	24	48	26.7
**Personality disorder**	6	No	24	48	22.3
**Total**			**236**	**472**	

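### The twelve-month arm comparison is labelled an effect of added sleep intervention, but controls are treated from six months, so it estimates early versus delayed start; only T1 compares with TAU alone

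*Protocol article*

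**What the plan says.** Under Procedure, the experimental arm starts the sleep intervention at T0. For controls, "In the control condition, the sleep intervention(s) will first start six months after inclusion, at T1 (TAU+SI-T1". Under Study outcomes, the hypothesis is set against TAU alone: "We hypothesize that the effect of added sleep intervention(s) will be larger than the effect of TAU alone in the TAU-SI-T1 group". Aims and objectives (objective 2), Design and Procedure also ask a second question, whether early treatment is beneficial.

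Under Effect of sleep disorder treatment, the effects of added sleep intervention "will be assessed at six and twelve months by comparison of treatment (TAU-SI-T0 and TAU-SI-T1) groups over time (T0, T1, and T2", using a separate linear mixed model for each outcome. Quality of life and general symptoms are analysed in the total population, and specific symptoms within the eight diagnostic groups. On covariates, "first results for crude models will be taken, after which models including potential confounders such as age, sex, and social demographic parameters are run". Randomisation is stratified by type of mental disorder (Procedure), but that factor is not among the covariates named.

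For the PANSS in schizophrenia spectrum disorder, "assessments will be made on positive and negative symptoms at T0 and T2".

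On sample size, "we aim at an effect size of 0.4" (Cohen's d). The section continues with "Power analysis based with an α of .05 and a power of .8" and arrives at a "required group size of 48 patients per diagnostic group (24 TAU+SI-T0 and 24 TAU+SI-T1". It does not say to which time point or contrast the effect size refers.

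**The concern.** TAU alone exists only between T0 and T1. After T1 both arms are offered the sleep intervention, so the T2 arm difference no longer contrasts having it with not having it. The analysis section nevertheless calls the six- and twelve-month comparisons by one name and gives neither priority. This is a matter of what the article states, not of detail left to an analysis plan.

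Two misreadings could follow. A small T2 difference, which is what an effective delayed intervention would produce, could be reported as evidence against the intervention. A significant overall group-by-time result could be reported as a lasting effect when it reflects controls catching up, or the reverse.

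**Working it through.** **Inputs from the article.** d = 0.4, α = 0.05, power 0.8, 24 per arm in six diagnostic groups, 46 per arm in two, and 236 per arm in total (2 × 46 + 6 × 24 = 236).

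**Assumptions, not in the article.** Two-sided testing. SD 1. The same correlation ρ between any two time points (0.5 unless stated). T1 questionnaires completed before controls start. A T1 difference of 0.4 SD that the early arm keeps. Controls recover a share c of it by T2.

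**Step 1: the plan's own figure.** The 48 does not follow from the stated inputs alone. Two independent means at d = 0.4 need 99 per arm. A repeated-measures group-by-time F test with three measurements and f = d/2 = 0.2 needs 42 in total at ρ = 0.5 and 50 at ρ = 0.4. So 48 is compatible with a three-time-point interaction test at an unstated ρ of about 0.42. The conclusion does not depend on this.

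**Step 2: what each time point contrasts.**

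| Time | Experimental arm | Control arm | Arm difference estimates |
|---|---|---|---|
| T1 | TAU + intervention | TAU alone | added intervention |
| T2 | TAU + intervention from T0 | TAU + intervention from T1 | early versus delayed start |

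**Step 3: the global test.** Take arm differences (0, a, b) at T0, T1, T2. The 2-df group-by-time test has noncentrality

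λ = n/[2(1 − ρ)] × (2/3)(a² − ab + b²), with n per arm.

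- Full catch-up, (0, 0.4, 0): a² − ab + b² = 0.16.
- No catch-up, (0, 0.4, 0.4): 0.16 − 0.16 + 0.16 = 0.16.

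The two are identical. With n = 236 and ρ = 0.5, λ = 236 × (2/3) × 0.16 = 25.2 and power is 99.7% in both cases. The test detects that something happened but cannot say which.

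**Step 4: the T0-to-T2 change contrast.** SE = √[(2/n) × 2(1 − ρ)] = √(2/236) = 0.092 at ρ = 0.5. The T2 difference is 0.4(1 − c).

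| Catch-up c | T2 difference | Power, T0 to T2 | Power, T0 to T1 | Power, 2-df test |
|---|---|---|---|---|
| 0 | 0.40 | 99% | 99% | 99.7% |
| 0.5 | 0.20 | 58% | 99% | 98% |
| 0.75 | 0.10 | 19% | 99% | 99% |
| 1 | 0 | 5% | 99% | 99.7% |

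The T0-to-T2 power depends on how well the delayed intervention works, although the effect of added intervention at T1 is 0.4 in every row.

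**Step 5: power for the T1 contrast.** Noncentral t, with the SD multiplied by √(1 − ρ²) when the T0 value is adjusted for.

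| Per arm | Unadjusted | ρ = 0.3 | ρ = 0.5 | ρ = 0.6 | ρ = 0.7 |
|---|---|---|---|---|---|
| 24 | 27% | 30% | 35% | 40% | 48% |
| 46 | 48% | 51% | 59% | 66% | 76% |
| 236 | 99.1% | 99.5% | 99.9% | >99.9% | >99.9% |

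Eighty per cent power needs 99 per arm unadjusted, or 90, 74, 63 and 51 per arm at ρ = 0.3, 0.5, 0.6 and 0.7.

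**The case against.** The strongest defence is that T2 is a sound randomised comparison for the early-treatment objective, and that six months is already planned. The analysis section names it, and the missing-data section foresees analyses of T0 against T1. A mixed model with categorical time yields the T1 contrast directly. All of this stands. What it does not answer is that one label is applied to both time points.

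Four stronger readings are tempting, and the documents do not support them:

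- *The planned analysis loses power.* Averaging T1 and T2, or fitting linear time, would dilute the effect, but the article specifies neither. The 2-df test keeps 98% to 99.7% power in the pooled sample. At 24 per arm and ρ = 0.5 it has 27%, the same as the T0-to-T1 change contrast. The rise to 35% in step 5 comes entirely from baseline adjustment, not from dropping T2.
- *Without baseline and stratum adjustment the result is biased.* An unadjusted randomised T1 contrast is also unbiased. The covariate list is open-ended, the stratum is constant within a diagnostic group, and the article does not say how T0 enters the model.
- *The T2 difference will be near zero.* That requires full catch-up. Controls begin with diagnostic work-up only at T1, so partial catch-up is plausible.
- *The schizophrenia spectrum group has no TAU-alone comparison.* This is true of the PANSS only. It supplements a short symptom questionnaire, and the section on specific symptoms schedules the questionnaires at all three time points.

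**Conclusion.** The point holds as one of labelling and estimand. The T1 arm difference answers the stated hypothesis against TAU alone. The T2 difference answers the early-versus-delayed question. The plan calls both an effect of added intervention, and its global comparison over time cannot separate them. The harm is mainly one of interpretation: a twelve-month null that full catch-up would produce could be read as failure. The T0-to-T2 figures of 58%, 19% and 5% show how far that can go, but they rest on assumed catch-up shares, ρ = 0.5 and a T1 effect of 0.4 SD. A reader might infer that T2 is invalid or that only T1 is worth analysing; the early-treatment objective rules that out.

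**What to change.** In the linear mixed model with categorical time:

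1. Name the T1 arm difference as the primary estimate of added sleep intervention versus TAU alone.
2. Report the T2 arm difference separately, as early versus six-month-delayed start. Use the PANSS for that second question only.
3. In the pooled analyses, adjust for the T0 value and the randomisation stratum (mental disorder), and make the crude model supportive. This gains precision; it is not a condition for validity.

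No new data are needed for this wording. The real cost is that the sample size section must restate disorder-specific power for the T1 contrast. At 24 per arm that is 27% to 48%, not 80%, so single-disorder results would have to be presented with that limitation, or the numbers reconsidered.

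This change does not cure the exclusions after randomisation (controls with a very severe sleep disorder referred at once, controls below the questionnaire cut-off at T1, unconfirmed sleep diagnoses). They can unbalance the arms at T1 as well as T2 and need separate attention.
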